## Abstract

**Astract:**

## Background

Evidence-based practice (EBP) has been defined as the *"conscientious, explicit and judicious use of current best evidence in making decisions about the care of individual patients" *[1]. The use of research evidence in clinical practice has been an area of interest in the health profession around the world [2,3]. The aims of using evidence to guide practice are to build a defensible body of clinical professional knowledge, and use the best available evidence to support effective practice in patient care [4]. Strategies have been continuously proposed and tested to enhance the application of research evidence in practice. However, across all health professions, the uptake of the evidence into clinical practice has been a common challenge, because to do so requires change and sustainable thinking, and behaviours [2]. Barriers such as lack of knowledge, skills, time, and access to the literature have been consistently reported [5-8], and strategies are continually being refined to address the range of barriers that confront clinicians wanting to implement research evidence into practice.

In developing countries, there are additional barriers in applying evidence into guide clinical practice. The diversity and culture of these countries have had significant impact on the type of health care provided, and the way in which it is delivered to patients. Generalising evidence developed in other countries may not always be appropriate, and summary evidence from systematic literature reviews is often not relevant and applicable to developing countries. For instance, a recent Cochrane review reported that there is no evidence that using tap water for wound cleansing increases infection [9]. There are no trials included in the review to represent the use of tap water in developing countries and thus, the evidence cannot be recommended in settings where a constant supply of potable tap drinking water is unavailable. Consequently, context-specific clinical trials that can represent scenarios in developing countries can also be difficult to conduct, due to limited knowledge, resources, funding, skills etc. Trials conducted in developing countries have often been found to be of poor quality because of lack of research training of the authors. Thus these trials may well be excluded in international systematic literature reviews, as they may not meet the criteria of high methodological quality [10]. As a result, out-of-date and even harmful practices are still being implemented in developing countries, despite evidence to the contrary from international research [11].

There is no simple answer to this scenario. However, a key solution to overcome these barriers has been considered to be effective education, training and peer support [10-13]. Researchers and clinicians in developing countries need more support to learn the concepts and acquire the skills related to evidence based practice, so that research and clinical practices improve. Thus there is an urgent need to build capacity for EBP knowledge and skills amongst health professionals in developing countries. The South East Asia Optimising Reproductive and Child Health in Developing Countries known as the SEA-ORCHID project, is one of the few research-based projects which builds on this need to train health professionals (doctors, nurses and midwives) in evidence-based practice [13,14]. This group tested the effectiveness of a multifaceted intervention designed to increase the capacity for EBP and research synthesis, of the health professionals involved in reproductive medicine. The authors reported that although there were difficulties encountered during the project, such as access to academic expertise when the health professionals returned to their countries and availability of resources (i.e. computers with internet connection), the project resulted in a greater understanding of EBP and development of skills related to EBP.

The impact of using evidence to guide clinical practice is also being explored in the field of allied health. Allied health has been defined by the United States Association of Schools of Allied Health Professionals (ASAHP) as "*professionals [being] involved with the delivery of health care related services pertaining to the identification, evaluation and prevention of diseases and disorders; dietary and nutrition services; rehabilitation and health systems management, among other*..." [15]. The National Health Service (NHS) Scotland classified allied health as "scientific, technical and therapy workers" [16]. More recently, a broader and three-dimensional classification of Australian allied health has been presented by Turnbull et al [17]. This classification is built on allied health groupings of therapies, diagnostic and technical, scientific and complementary services. Physiotherapy is an allied health profession classified in the therapy group, along with occupational therapy, psychology, podiatry etc. These professions provide treatment to manage a range of conditions, particularly musculoskeletal, neurological and respiratory. As developing countries rarely have either enough money to fund adequate health services, or enough health professionals to provide adequate treatment, treatment interventions should be underpinned by the concepts of EBP to ensure efficient, and effective services.

The application of the concepts of EBP in physiotherapy can be challenging. There are issues which concern the generalisability of the evidence from the literature to the population of interest and the nature of practice in some countries where physiotherapists are not first-contact practitioners. Based from unpublished works, medical doctors in the Philippines who specialize in rehabilitation medicine make decisions regarding the type of physiotherapy care that should be provided, and physiotherapists by tradition, follow these instructions [18]. The strong influence of this tradition on the nature of physiotherapy practice frequently makes it difficult for physiotherapists in the Philippines to modify their usual way of thinking and treating. Barriers have been consistently reported in the Western world that are specifically related to uptake of EBP by allied health practitioners, including lack of knowledge, skills, time, and access to the literature [5-8]. Anecdotally, these barriers are broadly at play in the Philippines. Moreover, in addition to cultural practices, updating current knowledge and practice for Filipino medical doctors and therapists is difficult due to lack of access to research information [12] that is directly applicable and practical to patients within the context of the local health care system.

Specific to the needs of a group of allied health professionals, namely physiotherapists in the Philippines, we designed and pilot-tested an EBP training program to enhance their knowledge, skills, attitudes and behaviour to EBP. This tailored, multifaceted EBP program builds on the concept of effective education, training and peer support as key solution to overcome barriers to EBP in developing countries. It is further underpinned by evidence from the literature on contents and strategies of effective EBP programs [19-22]. We conducted preliminary exploratory studies which established the nature and scope of physiotherapy practice in the Philippines, the needs of Filipino physiotherapists and their perspectives on teaching EBP to the Filipino physiotherapy population [18].

The planned intervention (the EBP program for Filipino physiotherapists) is a one-day evidence-based program using effective adult education strategies. It consists of short lectures, practical workshops and practice sessions. A detailed description of the program is attached in this protocol. The training program has been pilot-tested and assessed for feasibility and acceptability. The training program resulted in a large effect size (0.83) in terms of improving knowledge and skills to EBP. The participants reported in evaluation summaries and feedback, that the content of, and strategies used in, the training were effective and practical. This training was viewed by participants as a medium to update physiotherapy practice and bridge the gap between theory and actual practice.

## Methods

### Study Aims

There are two aims in this research project:

1. To assess the effectiveness of the EBP training program in improving knowledge, skills, attitudes and behaviour of Filipino physiotherapists; and

2. To provide a tested model of continuing education and uptake of evidence which is contextually relevant to Filipino physiotherapists, and which could be adapted readily for physiotherapists from other developing countries, and allied health professionals who are not first contact practitioners in any health care system.

### Study design and setting

#### Ethics

Ethical approval has been obtained from the University of South Australia's Human Research Ethics Committee (protocol no. 0000021872). The primary author is a PhD student at this university.

#### Design

The EBP training program will be tested using a randomised controlled design, using a waitlist control group.

#### Outcomes

Significantly improved knowledge, skills, attitudes and behaviour to EBP as measured by psychometrically sound instruments. A moderate effect size of >0.6 of the education program is anticipated, based from several trials synthesized in a systematic review [23].

#### Timing

The study will commence in January 2011 and finish in October 2011. A detailed time table is attached with this protocol.

#### Sample Size determination

To detect a "moderate" effect size (0.6) at 80% power and 5% level of significance (2 tailed distribution), the required sample size for each group (intervention and control) is 27 physiotherapists (calculated using standard sample size calculator software in MedCalc). We will test for a conservative (moderate) effect in our RCT, as we are uncertain whether the large effect size from the pilot study was an artefact of the small sample, or an example of a Hawthorne effect.

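### 27 per group gives about 58% power for an effect size of 0.6 at two-sided 5%, not the stated 80%; the stated inputs require 45 per group

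*Protocol article*

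**What the plan says.** The Design section sets up two randomised groups: "The EBP training program will be tested using a randomised controlled design, using a waitlist control group". The Sample Size determination section takes a standardised effect of 0.6 and states, for "80% power and 5% level of significance (2 tailed distribution), the required sample size for each group (intervention and control) is 27 physiotherapists", that the figure came from MedCalc. The same section says that 0.6 was chosen as a cautious value, because the large pilot effect may have been an artefact of a small sample or a Hawthorne effect. The Background reports that pilot result: "The training program resulted in a large effect size (0.83) in terms of improving knowledge and skills to EBP".

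The Outcomes section gives the expectation behind 0.6: "A moderate effect size of >0.6 of the education program is anticipated, based from several trials synthesized in a systematic review". The Plan of analysis compares changes between groups using means and 95% confidence intervals. Nowhere does the article state a one-sided test, a dropout allowance, a pre-post correlation or adjustment for baseline.

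**The concern.** The section gives every input of a standard two-group calculation and then an answer that does not follow from them. The gap is 17 or 18 participants per group, about 40% of the requirement, which is too large to come from rounding or from the choice between a normal and a t formula.

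Three things are at stake. The trial would present itself as having 80% power for a moderate effect when an unadjusted comparison has much less. A non-significant result could then be taken as evidence against a moderate effect, although the design had a substantial chance of missing one. And the stated reason for using 0.6, as protection against an inflated pilot estimate, would be largely lost.

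**Working it through.** **Inputs.** Standardised difference d = 0.6, power 80%, two-sided alpha 5% and 27 per group with equal allocation, all from Sample Size determination; two independent groups, from Design.

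**1. Can the plan's 27 be reproduced?**

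Normal approximation, per group:

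n = 2 × (1.960 + 0.842)² / 0.6² = 2 × 7.851 / 0.36 = 43.6, so 44.

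Two-sample t test (noncentral t): 44.6, so 45 per group, 90 in total.

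The stated figure is not reproduced.

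**2. Power with 27 per group.**

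- Noncentrality: 0.6 × √(27/2) = 2.205.
- Normal approximation: Φ(2.205 − 1.960) = Φ(0.245) = 0.597.
- Noncentral t with 52 degrees of freedom: 0.581.
- Chance of missing a true effect of 0.6: 1 − 0.581 = 0.419, about two in five.

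**3. Effect detectable with 80% power at 27 per group.**

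- Normal approximation: (1.960 + 0.842) × √(2/27) = 0.762.
- t test: 0.777.

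The t-test value is 0.18 above the planned 0.6 and 0.05 below the pilot 0.83.

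**4. Precision.** The 95% confidence interval for the difference has a half-width of about 2.007 × √(2/27) = 0.55 SD.

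**5. Could another reading give 27?**

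| Reading | Result | Supported by the text? |
|---|---|---|
| One-sided 5%, 80% power | 35.04, so 36 per group | No: two-tailed is stated |
| One-sided 5%, 70% power | 26.8, so 27 | No: neither is stated |
| Paired or one-group t test, d = 0.6 | 23.8, so 24 | No: two groups are sized |
| The same, with 10% dropout | 24/0.9 = 26.7, so 27 | No: neither is stated |
| d = 0.83 (pilot) | 23.8, so 24 per group | No: 0.6 is stated |
| The same, with 10% dropout | 24/0.9 = 26.7, so 27 | No: neither is stated |
| d = 0.78, two groups | 26.8, so 27 | No: 0.6 is stated |

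**6. Could use of the baseline score explain it?** Let ρ be the pre-post correlation, which the article does not give. With 0.6 expressed in raw SDs, the effective standardised effect is 0.6/√(1 − ρ²) under ANCOVA and 0.6/√(2(1 − ρ)) for change scores. Power at 27 per group:

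| ρ (assumed) | ANCOVA | Change scores |
|---|---|---|
| 0.3 | 62% | 45% |
| 0.4 | 66% | 51% |
| 0.5 | 70% | 58% |
| 0.6 | 77% | 68% |
| 0.7 | 86% | 80% |

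ANCOVA reaches 80% at about ρ = 0.64 (0.804). Change scores reach it at about ρ = 0.7 (0.798). If 0.6 is already expressed in SDs of change, a comparison of changes is an ordinary two-sample test and power stays at 58%.

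**7. Loss to follow-up (illustration only).** The article gives no dropout rate. If 15% were lost by three months, 27 × 0.85 ≈ 23 per group would remain and power for 0.6 would be 0.512.

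**The case against.** The best defence is that 58% depends on the analysis and on how 0.6 is standardised. The section does not say whether the SD is that of raw scores or of changes, or which procedure was run in MedCalc. Because the Plan of analysis compares changes, a high enough pre-post correlation could bring power to 80%. This is right as far as it goes: 58% must be labelled as the unadjusted two-sample figure, or the figure when 0.6 is in change-score SDs. It does not rescue the paragraph, because no correlation or adjustment is stated and change scores with a correlation below 0.5 would do worse than 58%.

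A second point is that the Outcomes section expects an effect above 0.6, where power is better: 71% at 0.7 and 77% at 0.75. That is also true, but the calculation is made explicitly for 0.6, and power is still below 80% at 0.75.

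Third, the planned confidence intervals would show a careful reader how imprecise the result is. That lessens the risk of misreading a null result but does not correct the stated power.

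Finally, detectability at 0.78 does not show that the pilot value was used in the calculation; 0.83 itself needs 24 per group and has 85% power at 27. The document does not reveal how 27 arose, and the finding does not depend on knowing.

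**Conclusion.** The concern holds. From the inputs stated in Sample Size determination, 45 per group are required (44 by the normal approximation), not 27. With 27 per group, an unadjusted two-sided 5% comparison has 58% power for 0.6 and 80% power only for about 0.78. The type II error at 0.6 is about 42%, roughly double the 20% stated.

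These figures assume two equal independent groups, all 54 participants analysed, and either no use of the baseline score or an effect expressed in change-score SDs. Baseline adjustment could close the gap, but only with a correlation that the article does not state. This is not detail left to a fuller document: the published inputs and the published result contradict each other. Since this is the article's only justification of sample size, it must be corrected.

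**What to change.** Rewrite the Sample Size determination paragraph so that the numbers agree. If 27 per group is kept, wording along these lines would do:

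> With 27 physiotherapists analysed per group, an unadjusted two-sample t test at the two-sided 5% level has 58% power for a standardised difference of 0.6 and 80% power for 0.78.

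The paragraph should also say which SD standardises the effect, and should drop or qualify the suggestion that the size is conservative relative to the pilot.

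If the authors want to claim 80% power for 0.6 with 27 per group, they should specify ANCOVA on the baseline score and state the assumed pre-post correlation, which has to be about 0.64 or higher. That value needs a source, such as the pilot data, and should not be chosen because it gives 27. The Adapted Fresno Test uses version 1 at baseline and version 2 after training, so the relevant correlation is the one between versions. The baseline assessments of knowledge, skills and attitudes are already scheduled, so no new data are needed for those outcomes. The Procedure describes no baseline diary, so this route does not cover the behaviour outcome.

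The cost is one corrected paragraph and, for the second route, one sentence in the Plan of analysis. Restating the power makes the claim accurate but does not raise the power. Reaching 80% without adjustment would take 45 per group, which is 2 × (45 − 27) = 36 more participants before any dropout allowance.

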#### Participant recruitment

Physiotherapists from hospitals and clinics in the Philippines will be recruited. Participants will be selected using the following criteria:

1. Licensed to practice physiotherapy and trained in the Philippines

2. Have not ever participated in any formal EBP training

#### Identification of reference population of participants

A register will be collated from a) a database of physiotherapists collated by the primary researcher from a preliminary study which established the profile of physiotherapists [18] and b) the registry of the Philippine Physiotherapy Association (PPTA), of which the primary researcher is a member and from whom approval has been sought and granted.

Physiotherapists who will express their interest in participating in the study will complete an information sheet which includes age, gender, years in practice, and highest educational attainment. There is also a screening component of the questionnaire which will seek information on any EBP training program. This section is particularly important as participants should not have been exposed to a formal EBP course or training to minimize the potential influence of such to the outcomes. To be specific, they should not have attended lectures and workshops on clinical question formulation, database searching, critical appraisal and applying findings on patient cases. Once screened for eligibility, participants will be asked to attend a meeting to orient them to the procedures of the study and to obtain written informed consents.

#### Randomisation and blinding

An independent researcher will randomly allocate participants into either the EBP training group or a waitlist control group, using a computer generated random numbers. Allocation into treatment and control groups will be undertaken by an independent research assistant who is unaware of the study objectives and the participants. The schedule of training will depend on the group allocation, such that those in the intervention group will have their training earlier than the waitlisted control group. Participants and assessors of the study outcomes will be blinded to the allocation at all times.

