**Figure 1 F1:**
[figure not shown]
**Flow of procedures**.

The EBP intervention group will attend a one day training (Additional File 1) in a training centre at the University of Santo Tomas, Philippines. The objectives of the training will be provided to the participants before each of the six lectures and the practical sessions. Small group discussions will occur between the lectures, to enhance learning opportunities for participants. A checklist to assist participants to apply the evidence developed for this study will be provided as a take-home recommendation form, to guide the application of evidence in actual patient cases (Figure 2). After the EBP training, a link to an online support will be introduced to the participants. This has been developed to assist the participants in their EBP-related activities post training, as follow up support and multifaceted interventions have more potential to influence clinicians' behaviour to using evidence in practice [2]. This online support is further described in the intervention section of this document. Activity diaries will also be provided to participants to log their EBP-related activities when faced with a new or unique case, and provide their comments to their activities for a period of three months for short term EBP behaviour assessment.

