**Figure 2 F2:**
[figure not shown]
**EBP Checklist**.

At the end of the training, participants will be asked to provide a second set of answers to the Adapted Fresno test and the Questions on attitudes to EBP for post EBP training intervention assessment.

The waitlist control group will undergo the pre and post- knowledge, skills and attitude test at the same period as the intervention group. There will be no training for the control group during this time. However, for the next three months, they will also be provided with activity diaries to log their activities as basis for their treatment when faced with a new or unique case, whether these activities are EBP-related or not.

Three months post EBP training, a third set of answers to the Adapted Fresno test and the Questions on attitudes to EBP, will be obtained from both groups to measure if knowledge, skills and attitudes to EBP were sustained over the three month period in the EBP intervention group and to measure the stability of knowledge, skills and attitudes to EBP of the control group.

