#### Questions to EBP attitudes

The Questions to EBP attitudes [25] will be used to assess the attitudes domain of EBP in this study. The attitudes to EBP scale consists of seven questions which are answered using a 3-point Likert scale: agree, neither agree nor disagree and disagree. The scale has been developed and validated for content and ease of completion [25]. In addition to this, participants will provide their comments on EBP and the EBP training program as part of this assessment.

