#### EBP behaviour

EBP behaviour will be measured in two ways: (1) activity diaries to be provided to all participants, both intervention and waitlist groups, in paper and electronic copies, and (2) frequency of logging in, in the online support for the EBP intervention training participants http://www.unisa.edu.au/cahe/Resources/EBPPhil/default.asp, considered as an electronic EBP learning portfolio. As it is not possible to conduct actual participant observation in practice, activity diaries are commonly used to log and report participants' activities in EBP [37]. The electronic EBP learning portfolio on the other hand, which according to the literature, are both educational intervention and an evaluation strategy," *is the most promising approach to document actual performance of EBP steps *"[37].

The frequency of conducting non-EBP (asking a peer, reviewing a textbook etc) and EBP-related activities (drafting a clinical question in PICO form, searching the literature for the evidence, undertaking critical appraisal and applying the evidence found) will be logged in the activity diaries provided to the participants. The frequency of conducting these activities and the frequency of logging in the online support provided will be counted and interpreted as behaviour measures. Behaviour measures will be interpreted in two ways, evidence-seeking behaviour and practice-change behaviours ref. Activities which relate only to drafting a clinical question, searching and appraising the evidence, are classified as evidence-seeking behaviours. Applying the evidence to an actual patient case is classified as a measure of practice-change behaviour [38].

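### Participants cannot be blinded against a waitlist, so the claim of blinding at all times is wrong, and attitude and diary results are self-reported by people who know their arm

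*Protocol article*

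**What the plan says.** The blinding statement under Randomisation and blinding has no qualifier as to person, outcome or time: "Participants and assessors of the study outcomes will be blinded to the allocation at all times". The sentence before it makes the training date depend on allocation: "those in the intervention group will have their training earlier than the waitlisted control group".

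The Design section names the comparator: "The EBP training program will be tested using a randomised controlled design, using a waitlist control group". The article describes no sham or attention course. Before the trial procedures start, "participants will be asked to attend a meeting to orient them to the procedures of the study and to obtain written informed consents" (Identification of reference population of participants).

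The Procedure section then separates the arms. For one, "The EBP intervention group will attend a one day training", followed by a take-home checklist and a link to online support. The other is tested over the same period, and "There will be no training for the control group during this time".

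Four measures are used. The Adapted Fresno Test covers knowledge and skills. For attitudes, "The attitudes to EBP scale consists of seven questions which are answered using a 3-point Likert scale". Behaviour is measured by activity diaries in both arms and by "frequency of logging in, in the online support for the EBP intervention training participants".

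**The concern.** A blinding statement tells the reader which biases the design controls. This one says that neither the people answering nor the people assessing know the allocation. If participants do know it, answers that depend on their own judgement or recording can shift with that knowledge. Someone just trained in EBP may express more favourable attitudes, or log more EBP activity, because that is what the course encouraged.

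The aim and the hypothesis cover attitudes and behaviour as well as knowledge and skills. A reader who trusts the sentence would treat between-group differences in all of them as protected from reporting bias. The planned intention-to-treat approach, means and 95% confidence intervals do not remove a bias that runs in one direction between arms.

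**Working it through.** No arithmetic applies. The article's design figures (27 per group, effect size 0.6) play no part in this point. The check sets the blinding sentence beside the procedures.

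**Step 1: what the claim requires.** For participants to be blind to allocation, they must be unable to tell from what happens to them which arm they are in. That needs a comparator resembling the intervention, or concealment of the difference.

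**Step 2: what participants experience.**
- Allocation fixes who is trained earlier and who later (Randomisation and blinding).
- Participants have been oriented to the study procedures (Identification of reference population of participants).
- The intervention arm attends a face-to-face day and receives the checklist and the online link (Procedure).
- The control arm answers the pre and post tests with no course between them (Procedure).

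At the post-training assessment each participant knows whether they attended. The baseline tools are emailed the day before the intervention group's course. Those attending have probably been given their date by then, so some may know their arm even at baseline; this last step is inference, and the conclusion does not need it.

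**Step 3: each measure in turn.**

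| Measure | Who produces the response | Who assesses it | Arms | What blinding can cover |
|---|---|---|---|---|
| Adapted Fresno Test | Participant | A rater; study researchers took part in the reliability check | Both | The rater, if scripts are coded |
| Attitude questions | Participant | The participant, by choosing a fixed category | Both | Nothing |
| Activity diaries | Participant | Whoever counts and classifies the entries | Both | The coder, as far as content allows |
| Login frequency | Participant's use of the site | Whoever counts | Intervention only | Nothing; the arm is known |

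**Step 4: limits on the rows where blinding is possible.**
- Diaries: EBP behaviour has activities counted and classified as evidence-seeking or practice-change. That step is separate from the participant's self-report and can be done on de-identified diaries. Content may still hint at the arm, because Procedure asks the intervention arm to log EBP-related activities and the control arm to log activities of either kind.
- Attitudes: comments on the training programme are collected in the same assessment and could disclose the arm to anyone handling the form.
- Fresno Test: blind rating protects against rater bias only. The person answering still knows their arm.

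**Step 5: count.** Participant blinding fails for four of four measures. Three of the four are collected in both arms and can be compared between them. Of those three, attitudes and diaries rest on self-report. Assessor blinding is attainable for the Fresno Test, partly attainable for diaries, not attainable for attitudes, and of no consequence to a between-arm contrast for logins.

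**The case against.** The best defence is that the arms are presented as earlier and later training, so participants might be blind to which schedule is experimental. That is conceivable, but the sentence says blinded to the allocation, and at all times. The article nowhere describes withholding the hypothesis or the status of the arms from participants.

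Other objections stand, and they limit the point. The article explains that direct observation of practice is not possible and that diaries are used for that reason, so the self-report nature of behaviour is disclosed; what is not disclosed is that the reporters know their arm. Login counts need little judgement and have no control-arm counterpart, so they show that the wording is too broad and not that a comparison is biased.

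A reader might also infer more than the document supports:
- *That only the Fresno scoring can be blinded.* Diary coding can be blinded in part, and declaring it unblinded would give up available protection.
- *That the Hawthorne remark under Sample Size determination shows bias in attitudes and diaries.* It concerns the pilot's large effect, which the Background reports (0.83) for knowledge and skills.
- *That the bias can be given a size.* A shift of 0.2 SD would be 0.2/0.6, one third of the target effect, but nothing in the document supports 0.2 or any other value.
- *That waitlisted participants have no incentive to report EBP activity.* They volunteered for an EBP study and keep diaries too.
- *That effectiveness should rest on the Fresno Test alone.* That would narrow the stated aim and does not follow from a wrong blinding sentence.

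**Conclusion.** The blinding sentence is wrong as written. Participant blinding is a property this design cannot have, and the article's own procedures contradict it. The assessor part is attainable for the Fresno Test and partly for diaries, so it needs narrowing and not removal.

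The consequence falls mainly on attitudes and diary behaviour. Their between-group differences carry a risk of reporting bias whose size cannot be derived from the document. The conclusion assumes only that attending, or not attending, a one-day course reveals the arm to the person concerned, and that no undescribed sham course exists. It does not depend on when the waitlist group is eventually trained, for which the article's text gives no date. Randomisation, sample size, instruments and planned comparisons are untouched by this point.

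**What to change.** Replace the sentence under Randomisation and blinding with wording to this effect: participants are not blinded to allocation; scorers of the Adapted Fresno Test are blinded, and so, as far as content allows, are the coders of the activity diaries.

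Make that workable:
- Remove identifiers and arm from Fresno scripts and diaries, give each a code, and pool both arms before scoring or coding.
- Use scorers and coders who neither teach the course nor run the online support.
- Keep the free-text comments on the training away from them.

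State that attitude and diary results are self-reported by unblinded participants, and that login counts describe the intervention arm only. Interpret attitude and diary differences between groups with that risk acknowledged. Keep every outcome named in the aim.

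The cost is a change of wording and a small amount of script coding. The drawback is that the stated blinding becomes less favourable.
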